## Abstract

**Introduction:**

Loneliness has increased substantially in the past decade and adversely affects the health and wellbeing of cancer survivors. Cancer diagnosis and treatment can lead to profound negative changes in health status and social support. In addition to prevention and detection of recurrence and new cancers, survivorship care also requires attention to managing financial, psychological, and physical wellbeing after cancer treatment. Multiple efficacious interventions exist for loneliness, including Social Prescribing, a UK-based model that supports individuals in improving their social connections. However, none have been adapted to meet the needs and preferences of cancer survivors.

**Design:**

This feasibility study protocol is reported according to the SPIRIT 2013 and 2025 statements. We adapted an efficacious Social Prescribing intervention to target loneliness in adult cancer survivors, using the ADAPT-ITT process. This protocol describes plans to conduct a feasibility study in preparation for a randomized controlled trial of the Enhanced Social Prescribing intervention. Participants will be randomized on a 1:1 ratio to usual care (brochure) or Enhanced Social Prescribing (intervention). We will recruit 36 participants from two rural and rural-serving primary care practices in the Northwest U.S.. Eligible individuals are age 18 or older, screen positive for loneliness on the 3-item UCLA Loneliness Scale, received a diagnosis of cancer in the past seven years, and speak English. The Enhanced Social Prescribing intervention meets one hour weekly for nine weeks. The primary outcome is participant-reported loneliness as measured by the UCLA Loneliness Scale. Secondary outcomes include participant reported social connection, self-efficacy, quality of life. Self-reported receipt of guideline concordant cancer survivorship care is an exploratory outcome. We will also measure Reach, Implementation, and Acceptability/Appropriateness of the Enhanced Social Support intervention. Using an intent to treat analysis, participants will be analyzed according to their assigned group. We will use linear mixed models to estimate differences between the intervention arm and control arm, and changes in outcomes over the study period. This study protocol is registered at clinicaltrials.gov (NCT07418437).

**Anticipated results:**

We anticipate successful recruitment of 36 participants and delivery of the Enhanced Social Prescribing intervention to 18 participants.

**Discussion:**

This study will demonstrate the feasibility of testing the Enhanced Social Prescribing intervention and provide preliminary data and procedures for a larger-scale randomized controlled trial to test the effectiveness and study the implementation of Enhanced Social Prescribing.

## Introduction

Loneliness has increased substantially in the past decade [1,2] and adversely affects the health and wellbeing of cancer survivors [3,4]. Loneliness is not a unitary construct, but a multidimensional, subjective experience encompassing distress related to perceived isolation, unmet emotional needs, and a lack of meaningful connection—regardless of the presence or absence of social contact [5]. Its prevalence in the U.S. is increasing; approximately one-third of the U.S. adult population reports feelings of loneliness [6]. Given that loneliness is associated with poorer overall mental and physical health, and risk of premature mortality, effective interventions to address loneliness are needed [7,8].

Cancer diagnosis and treatment can lead to profound negative changes in health status and social support [9,10]. An estimated 36% of the more than 18 million cancer survivors in the United States experience loneliness and social isolation [3]. Research demonstrates that cancer survivors who are racial/ethnic minorities and/or live in rural and underserved communities are even more likely to be lonely, suggesting interventions tailored to these populations may be needed [3].

Cancer survivorship care is complex and includes prevention and detection of recurrence and new cancers, monitoring and amelioration of symptoms related to cancer and its treatment, and management of chronic conditions. Cancer survivorship care also should address financial, psychological, and physical wellbeing after cancer treatment [3,11,12]. In the general population, loneliness is a major risk factor for common chronic medical conditions including hypertension [13–15], cardiovascular disease [16], heart failure [17], diabetes [18,19], obesity [18–20], depression [21], and cognitive decline [22]. Acknowledging cancer diagnosis, treatment, and survivorship as a chronic condition, this study will also explore the degree to which reducing loneliness may improve well-being and uptake of guideline concordant care among cancer survivors. Cancer survivors have unique sources of loneliness that may not be shared or understood by family members, friends, or the general community. These include cancer-related fears and worries, diagnostic and treatment concerns, and lack of or insufficient social support during their cancer treatment journey [23,24]. A systematic review and meta-analysis on loneliness in adult cancer survivors published in 2021 reported limited interventional studies to date on loneliness among cancer survivors [7]. Studies done since then have mostly been small, pilot studies and not tested with rural populations [25,26].

Multiple efficacious interventions exist for loneliness. A meta-analysis of interventions found efficacy in reducing loneliness through interventions that improved social skills, enhanced social support, and increased opportunities for social contact [27]. Building from the evidence and recognizing the substantial problem of loneliness on health, the 21st U.S. Surgeon General, [name], published an advisory on the loneliness epidemic that highlights three vital components of social connection: structure, function and quality [1,2]. Structure refers to the type, number and variety of relationships; function refers to the ways in which relationships serve an individual’s various needs (e.g., emotional, social and/or spiritual); and quality refers to the positive and negative aspects of relationships and interactions and how it is perceived by the individual. This model is adapted from Holt-Lunstad’s framework for understanding why social relationships are important for mental and physical health [28]. Social prescribing is a United Kingdom-based model to address loneliness [29]. In social prescribing interventions, patients are referred by general practitioners and then partner with lay and/or peer workers to develop personalized strategies to improve support and connection [30–35]. While evidence supports its’ efficacy, social prescribing has not been applied widely outside the United Kingdom and Europe [34,35]. Furthermore, it has not been tested specifically for adult cancer survivors with loneliness.

The aim of this study is to conduct a feasibility pilot randomized controlled trial to test, in adult cancer survivors who receive care in rural and rural-serving primary care practices, a loneliness intervention that draws on the principles of social prescribing. We will enroll 36 adult cancer survivors who are experiencing loneliness, and who will be randomized to either Enhanced Social Prescribing (n = 18) or usual care (n = 18). We will collect outcomes on loneliness, social connection, self-efficacy, quality of life, and quality of cancer survivorship care. Our goal is to improve overall wellness and quality of life among cancer survivors and demonstrate pilot efficacy of a novel, adapted program that may improve survivorship care outcomes.

## Methods

The approved study protocol is provided in Supplement 1

### Trial status and timeline

This study protocol is registered at clinicaltrials.gov (NCT07418437). As of March 2026, we have begun enrollment of participants. Full enrollment is anticipated by 9/30/2026. All data collection is anticipated to be completed by 12/31/26. Results of primary outcomes analysis is expected by 3/31/2027. The timeline of study data collection is provided in Supplement 3.

Prior to the feasibility study, we engaged adult cancer survivors to collaboratively adapt an intervention, building on the social prescribing model and using the ADAPT-ITT framework [36]. The Enhanced Social Prescribing intervention builds on the social prescribing model and also includes psychosocial educational support and is delivered in a group setting.

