### Design

This feasibility study protocol is reported according to the SPIRIT 2013 and 2025 statement [37,38]. The SPIRIT checklist is provided in Supplement 1. We used the ADAPT-ITT process to conduct an intervention adaptation phase will follow with a randomized controlled trial (RCT) to test an Enhanced Social Prescribing intervention that targets loneliness in adult cancer survivors. We engaged adult cancer survivors and topical experts to adapt the intervention for a feasibility study. ADAPT-ITT is an 8-step approach to adapting existing evidence-based interventions to novel populations. The steps include: 1) Assessment, 2) Decision, 3) Administration, 4) Production, 5) Topical Experts, 6) Integration, 7) Training and 8) Testing [36]. The methods and results of the adaptation and intervention development phase will be reported separately.

Consistent with principles of hybrid implementation designs [39], this feasibility study prioritizes implementation outcomes—feasibility, acceptability, and appropriateness—while collecting preliminary clinical outcome data. Participants will be randomized on a 1:1 ratio to usual care (brochure) or Enhanced Social Prescribing (intervention). Outcome measures will be completed at baseline, 9 weeks (immediately post-intervention), and 17 weeks following study entry.

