#### Consent, Randomization, concealment of allocation, and blinding.

Interested potential participants will schedule a telephone call with the research coordinator to learn more about the study. After confirming study eligibility and sharing consent information, the research coordinator will obtain the participant’s verbal informed consent to participate in the study. Following verbal consent, participants will be sent an electronic survey via REDCap to review the full electronic consent information form and then subsequently complete the baseline survey. Participants will be required to review the electronic consent information form prior to initiating the baseline line survey. If participants prefer to, they may elect to complete the baseline survey over the phone with the research coordinator. Participants will be considered enrolled in the study upon completion of the baseline survey. After enrollment, a research coordinator responsible for enrollment and study operations but not involved in data collection or analysis will randomize them in a 1:1 ratio to either Enhanced Social Prescribing intervention or enhanced usual care using random permutated blocks [43]. Randomization will be conducted using REDCap. Procedures to ensure allocation concealment include using parallel structures in REDcap for each arm, which reduces the possibility that study personnel interacting with the database can infer treatment assignment.

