We will continue the recruitment strategies above until we reach our goal of 36 participants enrolled. Participants will be allocated to one of two study arms of roughly equivalent size. Recruitment for this study opened on 15/03/2026 and will last for six months (14/09/2026) or until recruitment target (n = 36) is reached, whichever comes first.

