**Fig 2 pone.0350956.g002:**
[figure not shown]
Study consort flow diagram.

We will collect the outcome measures from patients at 9 and 17 weeks after enrollment via REDCap survey. The research coordinator will conduct additional outreach, including telephone, text message, email, and written communication according to each participants’ preference to ensure complete data collection. Participants will receive USD 25 for completing each outcome assessment. Participants will be analyzed using an intent to treat analysis and included in primary outcomes analysis even if baseline data are missing. Missing data will be described to assess the amount, patterns, and reasons for missigness. Any variable with substantial missigness will undergo careful review before being considered as a candidate variable for future trials.

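### The anticipated end of data collection (31 December 2026) comes before the 17-week survey is due for anyone enrolled after 3 September 2026

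*Protocol article*

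**What the plan says.** The relevant dates are spread over several sections of the protocol article.

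- **End of data collection** (Trial status and timeline): "All data collection is anticipated to be completed by 12/31/26".
- **Enrollment target date** (same section): "Full enrollment is anticipated by 9/30/2026".
- **Recruitment period** (Recruitment): "Recruitment for this study opened on 15/03/2026" and it "will last for six months (14/09/2026) or until recruitment target (n = 36) is reached, whichever comes first".
- **Assessment times** (Design): "Outcome measures will be completed at baseline, 9 weeks (immediately post-intervention), and 17 weeks following study entry". The data collection text under Procedure agrees: "We will collect the outcome measures from patients at 9 and 17 weeks after enrollment via REDCap survey".
- **Start of the clock** (Consent, Randomization, concealment of allocation, and blinding): "Participants will be considered enrolled in the study upon completion of the baseline survey".

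The timeline section expects primary results by 31 March 2027. Two figures for completeness of follow-up appear. The Implementation part of the statistical analyses sets at least 90% of participants completing all data collection points. Expected findings anticipates at least 70%.

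**The concern.** The timeline section puts full enrollment at the end of September and the end of all data collection at the end of December, roughly three months later. The final assessment comes 17 weeks after enrollment, which is nearly four months. Someone enrolled near either closing date would therefore have a final survey due after the stated end of data collection, before any time for reminders.

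What is at stake is the 17-week outcome of the latest enrollees. Completeness of follow-up data is a named feasibility outcome, and the study is meant to inform the design of a larger trial. If the calendar were followed literally, some missing 17-week surveys would be produced by the timetable and could be read as poor retention.

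**Working it through.** **Inputs.** Recruitment opens 15 March 2026 and closes 14 September 2026 (Recruitment). Full enrollment is anticipated by 30 September 2026, and data collection ends 31 December 2026 (Trial status and timeline). Follow-up is at 9 and 17 weeks from enrollment (Design; Procedure). The target is 36 participants.

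**Step 1: can the stated end date be reproduced?** Last survey due = last enrollment date + 17 × 7 = 119 days.

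| Last enrollment | 9-week survey due | 17-week survey due | Days after 31 Dec 2026 | Weeks from last enrollment to 31 Dec |
|---|---|---|---|---|
| 14 Sep 2026 | 16 Nov 2026 | 11 Jan 2027 | 11 | 15.4 |
| 30 Sep 2026 | 2 Dec 2026 | 27 Jan 2027 | 27 | 13.1 |

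Neither closing date leaves 17 weeks, so the stated end date is not reproduced. The 9-week survey fits in both cases.

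**Step 2: latest enrollment that fits.** 31 December 2026 − 119 days = 3 September 2026. Enrollment on 4 September gives a survey due on 1 January 2027. The 11 and 27 January dates apply to people enrolled on the closing dates themselves.

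**Step 3: how many participants?** The article gives no accrual forecast, so uniform accrual of 36 participants from 15 March is assumed. Expected number enrolled after 3 September = 36 × (days after 3 September) / (days of accrual, both ends counted).

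- Closing 14 September: 36 × 11/184 = 2.15, about 2.
- Closing 30 September: 36 × 27/200 = 4.86, about 5.

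Back-loaded accrual would raise these numbers, and early completion of enrollment would lower them to as few as zero.

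**Step 4: against the completeness figures.** These assume that every survey due after 31 December is left uncollected and that there is no other loss.

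- The 90% benchmark: 0.90 × 36 = 32.4, so 33 completers are needed and at most 3 may be lost.
  - Losing 2 leaves 34/36 = 94%. The benchmark is met, with room for one further loss.
  - Losing 5 leaves 31/36 = 86%. The benchmark fails for calendar reasons alone.
- The 70% anticipation: 0.70 × 36 = 25.2, so 26 completers are needed and up to 10 may be lost. Neither case threatens it.

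**Step 5: room before reporting.** From 27 January 2027 to 31 March 2027 is 63 days.

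**The case against.** The strongest reply is that the end date is a forecast. It is worded as anticipated, it is not a database lock, and no section says that a survey due in January would be left uncollected. The Procedure section commits to telephone, text, email and written outreach to obtain complete data, and results are not expected until 63 days after the latest due date. On this reading the forecast simply slips by 11 to 27 days. Recruitment also stops once 36 are enrolled, and if that happens by 3 September nobody is affected. All of this stands. It removes any claim of certain loss, but the printed dates still do not fit together if enrollment runs to either closing date.

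Three stronger readings are tempting but unsupported.

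- A reader might infer that the last participants will lose their final outcome. That needs both enrollment past 3 September and a hard stop on 31 December, and the article states neither.
- A reader might infer that the shortfall counts against a progression criterion. Table 1 covers enrollment, baseline data, drop-out and intervention delivery, but not completeness of follow-up. A survey that was never sent is not plainly a drop-out.
- A reader might infer that the late enrollees would all sit in the last intervention group. With 1:1 randomization, about half would be in usual care.

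It can also be said that 14 and 30 September are compatible: recruitment closes first, and consent calls and baseline surveys take up to 16 days more. That is plausible, though the article does not say so, and under that reading the later due date of 27 January applies.

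The effect on the analysis is also limited. A participant with a 9-week value can still contribute to the mixed model, and the study is not powered for effectiveness. Supplement 3, which holds the data collection timeline, is not at hand. It may clarify the intention, but it cannot make the dates printed in the article agree.

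**Conclusion.** The inconsistency is real and its severity is minor. The arithmetic is certain: anyone enrolled after 3 September 2026 has a 17-week survey due in January 2027, as late as 11 January for a 14 September close or 27 January for a 30 September close. The consequence is conditional. Only if enrollment runs to those dates and 31 December is enforced would about 2 to 5 of 36 participants miss the 17-week survey, and those counts rest on assumed uniform accrual. In the 30 September case the 90% benchmark would fail on the calendar alone. In the 14 September case it would not, and the 70% anticipated under Expected findings is safe in both. The documents do not show that data will be lost.

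**What to change.** Give one closing date for enrollment in both Trial status and timeline and Recruitment, or state that the later date allows people already recruited to complete baseline. Then do one of the following:

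- Set the end of data collection to at least the last enrollment date plus 17 weeks plus the outreach window. Before outreach, that means 11 January 2027 or 27 January 2027, depending on the closing date chosen.
- Keep 31 December 2026 and close enrollment by 3 September 2026 less the outreach window.

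It would also help to state that every 17-week survey will be collected whatever the calendar date.

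The cost is a change of dates in the protocol and in any registry or ethics record that repeats them. The second option shortens recruitment. With the first, the 31 March 2027 results date need not change, provided that the outreach window and the analysis fit within the 63 days after 27 January.

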### Design

This feasibility study protocol is reported according to the SPIRIT 2013 and 2025 statement [37,38]. The SPIRIT checklist is provided in Supplement 1. We used the ADAPT-ITT process to conduct an intervention adaptation phase will follow with a randomized controlled trial (RCT) to test an Enhanced Social Prescribing intervention that targets loneliness in adult cancer survivors. We engaged adult cancer survivors and topical experts to adapt the intervention for a feasibility study. ADAPT-ITT is an 8-step approach to adapting existing evidence-based interventions to novel populations. The steps include: 1) Assessment, 2) Decision, 3) Administration, 4) Production, 5) Topical Experts, 6) Integration, 7) Training and 8) Testing [36]. The methods and results of the adaptation and intervention development phase will be reported separately.

Consistent with principles of hybrid implementation designs [39], this feasibility study prioritizes implementation outcomes—feasibility, acceptability, and appropriateness—while collecting preliminary clinical outcome data. Participants will be randomized on a 1:1 ratio to usual care (brochure) or Enhanced Social Prescribing (intervention). Outcome measures will be completed at baseline, 9 weeks (immediately post-intervention), and 17 weeks following study entry.

### Setting

The WWAMI (Washington, Wyoming, Alaska, Montana and Idaho) region Practice and Research Network (WPRN) is a practice-based research network of approximately 140 primary care practices across the 5-state region that agree to be engaged in relevant research. The practices include federally qualified health centers, rural health centers, large health systems and private practices and serve a diverse group of patients. To ensure participation from rural cancer survivors, we elected to invite all rural and rural-serving primary care practices in the WPRN to consider participating. Invitations to participate were shared electronically with champions (physician representatives to the WPRN) from each eligible rural or rural-serving health system (n = 19). Champions were instructed to respond by email with interest. The study PI and research coordinator met with interested champions (4) to share more details about the study and affirm interest/eligibility. Three interested sites affirmed willingness and capacity to support recruitment and two enrolled in the study. We limited participation to two sites based on anticipated sample size and feasibility. The practices will be reimbursed for their work with recruitment, engagement, and data provision/collection.

### Sample size calculation

Because this is a feasibility pilot study, no sample size calculations were performed. 36 participants was selected as an enrollment goal based on ensuring sufficient enrollment for at least two cohorts for the enhanced social prescribing intervention and matching enrollment to the available resources and timeline. The estimates of baseline and outcome measures from this study will be used to calculate sample size for a full-scale trial.

### Characteristics of participants and eligibility criteria

This study will include 36 participants who are 18 years of age or older at the time of enrollment, screen positive for loneliness (score of ≥ 6 on the 3-item UCLA Loneliness Scale), received a diagnosis of cancer in the past seven years, speak English, and have had a primary care clinic visit at one of the partnering primary care organizations in the past two years. The 3-item UCLA Loneliness Scale is a validated screening survey that asks about feelings of lack of companionship, feelings of being left out, and feelings of isolation from others [40]. Each item is scored on a scale of 1–3 with total score ranging from 3–9. We chose the 3-item screener instead of the 20-item UCLA Loneliness Scale because it can pragmatically be used in care settings, and we have successfully used this scale for clinic-based and text-based recruitment in previous studies [41,42].

We will exclude patients who are currently living in an inpatient or rehabilitation setting, have scheduled or planned surgery or inpatient hospital admission in the next 3 months, have severe or moderate cognitive impairment or active psychosis.

